## Abstract

**Background:**

With increasing human longevity there is increasing prevalence of osteoporosis and of osteoporotic vertebral fractures. Most vertebral fractures do not require medical therapy for pain, but a minority are associated with severe pain and disability.

Vertebroplasty has been used increasingly for painful acute osteoporotic fractures. The best available evidence for vertebroplasty is provided by two placebo controlled trials which showed no significant clinical benefit of vertebroplasty over placebo. These were not acute fracture trials with the majority of fractures in both trials being well beyond the acute time frame of 6 weeks. There is evidence from an open label randomized controlled trial of vertebroplasty versus conservative therapy in acute fractures suggesting clinical efficacy in acute vertebral fractures.

**Methods:**

This is a blinded trial of Vertebroplasty for Acute Painful Osteoporotic fractURes - the VAPOUR trial. Patients greater than 60 years in age with new severe onset of back pain and osteoporotic vertebral fractures of less than 6 weeks duration will be enrolled. They will be randomized to receive either vertebroplasty or a placebo procedure. Data regarding pain, disability, and quality of life will be collected over a 6-month period. The enrolled patients and the outcome assessors will remain blinded for the duration of the trial.

**Discussion:**

The VAPOUR trial will apply similar methodology to the previous blinded trials but in a patient group with exclusively acute fractures and the most severe pain.

**Trial registration:**

ClinicalTrials.gov trial identifier: NCT01482793 registered on 28 November 2011.

## Background

With increasing human longevity there is increasing prevalence of osteoporosis. Vertebral body fractures are among the most common osteoporotic fractures. Whilst most cause minimal symptoms, a subset can cause severe acute fracture pain. Vertebroplasty has become a commonly used procedure for the management of painful osteoporotic vertebral fractures.

There is conflict in the best published evidence for vertebroplasty. There are two blinded randomized controlled trials (RCTs) published together in 2009 [1,2] which provide the highest quality evidence at present and show no benefit of vertebroplasty over placebo at any time point. Both enrolled similar patient groups, with osteoporotic fractures and back pain for up to 1 year. The average durations of back pain in these trials were 16 to 18 weeks in the larger trial [1] and 10 weeks in the smaller trial [2]. Neither trial found significant clinical advantage over placebo in the vertebroplasty group at any time point.

The largest open label RCT of vertebroplasty [3] limited enrolment to painful fractures less than 6 weeks duration. This trial compared vertebroplasty to usual care and found positively for vertebroplasty with enhanced reduction in pain score and also in the Roland Morris Disability score in the vertebroplasty group at each time point out to 12 months following the intervention. Similar findings were obtained in a large open label RCT of kyphoplasty versus conservative therapy [4] in a patient group with fracture pain less than 3 months duration.

A debate developed regarding the apparent discrepancy in findings between the blinded and the open label trials. Proponents of vertebroplasty argued that patient selection and procedural technique explained the negative findings in the blinded trials [5,6]. The Vertos II trial [3] was a trial of vertebroplasty for acute fractures whereas the two blinded trials [1,2] included predominantly non-acute fractures where the bone may have already healed. Patient selection could explain the difference. Technical considerations, and in particular the small volume of cement injected, were also questioned in the blinded trials [7]. Conversely, evidence-based medicine experts have argued that the design of the blinded trials was superior and that the apparent efficacy of vertebroplasty in the Vertos II trial was due to a placebo effect and the inherent bias in an open label trial [8-10].

A meta-analysis [11] of the two blinded RCTs attempted to answer the remaining question about the efficacy of vertebroplasty in the acute setting. The authors found 57 patients (25 vertebroplasty and 32 controls) from the combined enrolment of both blinded RCTs [1,2] to have had back pain for less than 6 weeks. This meta-analysis found no benefit of vertebroplasty over placebo at one week or one month. Analysis beyond one month was not presented. This meta-analysis contained little technical data with no reporting of the vertebral fracture levels, the inclusion of inpatients or not (inpatients were completely excluded in the larger trial and not reported in the smaller trial), and the cement volume injected (average 2.6 cc for both trials overall, but no reporting for this sub-group meta-analysis).

There is clearly a requirement for a resolution of the conflicting clinical evidence for vertebroplasty in the acute fracture setting. This requires a blinded RCT of vertebroplasty for acute vertebral fractures (defined as less than 6 weeks duration) with new onset of severe back pain (defined as pain score greater than 7/10). We are conducting such a trial: Vertebroplasty for Acute Painful Osteoporotic vertebral fractURes (The VAPOUR Trial).

### Mechanics of vertebroplasty

The mechanics of vertebroplasty underpin the treatment’s application and patient selection, and these principles need be clarified as they affect study design. We hypothesize that vertebroplasty is only effective when applied in the acute fracture setting in patients with severe pain. It can then potentially provide internal fixation and ameliorate the acute pain generated by fracture fragment motion. To achieve adequate internal fixation in a collapsing bone, we believe that the volume of injected cement is important to outcome and this volume will be measured. We also hypothesize that fractures in different parts of the spine are subject to different biomechanical forces which affect fracture behaviour. These segments may therefore respond differently to vertebroplasty. We will analyze the sub-groups of thoracic (T4-T10), thoraco-lumbar (T11-L2) and lumbar (L3-L5) as categorized in previous RCTs of spinal augmentation [3,4]. It is our anecdotal belief that the thoraco-lumbar segment is the region of the spine that responds best to vertebroplasty in the acute setting. This is the segment that is exposed to the largest flexion forces and accounts for the majority of “osteonecrotic” fracture clefts filled with either fluid or gas [12-14]. It has been previously demonstrated that thoracolumbar fractures are predisposed to “dynamic mobility” [15] which means that the vertebral body assumes different volumes in the erect and supine (or prone) positions. Such a fracture should benefit the most symptomatic relief from internal fracture fixation afforded by vertebroplasty by reducing fracture fragment motion.

The thoracic vertebrae (T4 to T10) undergo relatively reduced flexion force due to the bracing of the posterior elements by the rib cage. The reduced force across the fracture line in the thoracic segment may imply that natural healing is improved and that less mechanical advantage is obtained from vertebroplasty.

## Methods/design

### Trial design

The trial is a participant and outcome-assessor blinded randomized controlled trial of vertebroplasty for acute fractures. Acute fracture will be defined as new severe onset of back pain (of less than 6 weeks duration) associated with magnetic resonance imaging (MRI) or single-photon emission computed tomography (SPECT)-computed tomography (CT) evidence consistent with a recent fracture. MRI or SPECT-CT must be obtained within a week of patient enrolment. The MRI will include sagittal T1 weighted and fat suppressed T2 weighted images of the thoracic and lumbar spine. Deformity of the vertebral body associated with the high signal pattern (T2) and low signal pattern (T1) of acute fracture within the vertebral body will define recent fracture. Note that the precise duration of fracture is defined by careful questioning of the patient as to the date of onset of severe pain. The pain location should be consistent with the recent fracture identified on MRI. When MRI is contraindicated, then SPECT-CT will be obtained. Increased radioisotope uptake in the pattern of recent fracture associated with fracture deformity of the vertebral body will be accepted as evidence of recent fracture.

The trial is of essentially similar design as the previous two blinded RCTs [1,2]. It is a multicentre trial involving four centres in Sydney, Australia that have established vertebroplasty programs. Data will be collected at baseline, 3 days, 2 weeks, 1 month, 3 months and 6 months post intervention. The patient and the data collectors remain blinded for the duration of the trial.

### Patient selection

Patients referred for vertebroplasty will be screened for eligibility according to principle inclusion and exclusion criteria (Table 1). Those patients who are eligible for enrolment will be offered entrance into the trial. Vertebroplasty will not be available outside of the vertebroplasty trial, so that eligible patients are offered the choice between conservative care and enrolment in the trial. Ineligible patients will not be offered vertebroplasty. The conflicting evidence for the role of vertebroplasty in the management of acute osteoporotic fractures will be explained to the patient by the referring physician and the interventional radiologist. Informed consent to participate in the trial will be obtained prior to patient enrolment.

**Table 1 Tab1:** **Principle inclusion and exclusion criteria**

**Inclusion criteria**	**Exclusion criteria**
Age >60	Inability to provide informed consent
Pain from one or two acute vertebral fractures	Chronic back pain requiring narcotic analgesia
MRI or SPECT-CT obtained within previous week	Presence of sciatica
Duration of fracture pain <6 weeks	Significant retropulsion into spinal canal
Pain >7/10 on numeric scale	Evidence of spinal malignancy
Patient can speak English	Active systemic infection

### Baseline assessment

After the patient has consented to inclusion in the trial, baseline medical history including general medical history, history of osteoporosis, previous fractures, previous spinal interventions and medications is recorded. Baseline measure of numeric pain scores and visual analogue pain scores are collected together with Roland Morris Disability score, QUALLEFFO quality of life, medication usage and EQ-5D. The baseline assessment is collected either on the day of the procedure or the day prior to the procedure, depending upon patient convenience.

### Random allocation

The subjects will be randomized to either the control intervention group or the vertebroplasty group using the method of minimization. This will be performed centrally at the National Health and Medical Research Council (NHMRC) Clinical Trials Centre, University of Sydney. The call to the NHMRC Clinical Trials Centre will be made once the patient is in the procedure room immediately prior to the procedure.

Randomization will be 1:1 to each treatment arm, and patients will be stratified by the following factors: * Age (<75, ≥75 years) * Degree of bone height loss (<50%, ≥50%) * Fracture due to trauma (Yes, No) * Patient taking steroids (Yes, No) * Hospital/site.

### Procedures

Patient will be laid prone on the procedure table and an oxygen mask applied. Pulse oximetry monitoring will be used continuously to monitor arterial oxygen saturation and pulse rate. Conscious sedation, comprising midazolam and fentanyl, will be administered intravenously.

Vertebroplasty will be performed according to the standard practice of the Interventional Radiology investigators in the trial. Local anesthetic will be injected into the soft tissues of the back and a 4-mm skin incision made to allow entrance of the vertebroplasty needle. An 11-gauge or 13-gauge vertebroplasty needle will be introduced into the vertebral body using a transpedicular approach and fluoroscopic imaging guidance. Either a unipedicular or bipedicular approach can be employed depending upon operator preference. AVAMAX (CareFusion Corporation) bone cement will be used for all vertebroplasty procedures. The cement is injected into the vertebral body using the approved kit technique during continuous fluoroscopic screening. The injection will be terminated when there is satisfactory distribution of the cement or if there is any cement leak into an adjacent structure. The proceduralists have been advised to attempt “maximal fill” of the vertebral body where possible. Ideally this means a cement distribution from the superior to the inferior end plate, from the medial cortex of the pedicle to the medial cortex of the contralateral pedicle and from the anterior cortex of the vertebral body to the posterior third of the vertebral body. Cement injection is always performed in the lateral screening projection with intermittent fluoroscopic checking in the anteroposterior (AP) projection. When these fluoroscopic end points are achieved in the AP and lateral projections, the injection is ceased. If there is significant venous, disc or spinal canal cement extrusion observed, then the injection is terminated. The vertebroplasty kits used in this trial include an injecting syringe with clear volumetric markings which facilitates volume measurement. The volume of cement injected in each vertebroplasty case will be recorded accurately.

The control intervention is designed to simulate the procedural patient experience of a vertebroplasty. After administration of conscious sedation, local anesthetic will be injected into the subcutaneous tissues of the back in the vicinity of the fracture. A 4-mm skin incision is made and light tapping on the skin will be made to simulate vertebroplasty needle advance. Conversation regarding cement mixing and injection will be made by the operator to suggest a vertebroplasty is being performed.

### Measures

Data will be recorded at baseline, 3 days, 14 days, and 1, 3 and 6 months following procedure. During the baseline consultation patient questionnaires will be administered in a face-to-face interview. The 2-week and 6-month interviews will also be conducted in person by research staff during patient visits. The other interviews (day 3, month 1 and month 3) will be conducted by the same research staff by telephone. An exception to this will be inpatients that remain in hospital at day 3 who may be interviewed at bedside. The schedule of these data points is presented in Table 2.

**Table 2 Tab2:** **Schedule for data collection**

**Evaluations**	**Visit baseline**	**Phone day 3**	**Visit day 14**	**Phone 1 month**	**Phone 3 month**	**Visit 6 month**
Procedure/operative information	X					
Pain NRS Questionnaire	X	X	X	X	X	X
Pain VAS Questionnaire	X		X			X
Physicians VAS Questionnaire	X		X			X
Roland-Morris Low Back Pain and Disability Questionnaire	X	X	X	X	X	X
Osteoporosis Quality of Life Questionnaire (QUALEFFO)	X		X	X		X
EQ-5D Questionnaire	X	X	X	X	X	X
Change in pain		X	X			
Perception of treatment assignment		X	X			
Pain medication	X	X	X	X	X	X
Timed up and go test	X		X			X
Adverse events		X	X	X	X	X
Resource use/health care utilization information						X
Erect spinal X-ray	X					X

The numeric rated scale (NRS) of pain will be used at all data collection points. Patients will be asked to answer with a number between 0 to 10 to estimate their pain intensity. This is the primary outcome measure. To standardize results, the primary pain question is the same as that used in the INVEST Trial [16], the larger of the published blinded trials of vertebroplasty. This primary pain score will record pain over the previous 24 hours. Separate numeric pain scores at rest and during standing or moving will also be obtained.

Visual analogue scale (VAS) of pain will be recorded at the three clinic visits (baseline, 2 weeks and 6 months post procedure). This score will be obtained by asking the patient to make a mark on a line which is 10 cm in length in answer to the primary pain question. The line is marked “no pain” at the left extreme and “worst possible pain” at the right extreme. There are no other divisions or marks on the line. This VAS measure is recorded for overall pain over previous 24 hours as well as separate measures for pain at rest and during walking or activity. This VAS pain score will supplement the NRS pain score at these three time points including the primary end point (NRS pain at 2 weeks post procedure). The subjective nature of patient reported pain is problematic and thus the dual pain measurements. The researcher will also record their own estimate of patient pain at the clinic visits.

The Roland-Morris Low Back Pain and Disability Questionnaire (RDQ) is a 24-item back pain specific functional status questionnaire [17]. It consists of 24 yes/no items, which represent common dysfunctions in daily activities experienced by patients with back pain. Scores range from 0 to 24, with higher numbers indicating worse physical functioning. This score will be collected at all data collection time points.

The Quality of Life Questionnaire of the European Foundation for Osteoporosis (QUALEFFO) comprises 41 quality of life questions and includes five domains: (A) pain; (B, C, D) physical function; (E) social function; (F) general health perception and (G) mental function [18]. The physical function domain is separated into three sub-domains: activities of daily living (B), jobs around the house (C) and mobility (D), so there are effectively seven categories. Each of these seven categories will be individually scored in addition to an overall score. This questionnaire is quite time consuming and lengthy for the elderly, frail patients in this trial. For this reason it will be administered at baseline, 2 weeks, one month and 6 months but not at 3 days and 3 months.

The European Quality of Life - 5 Dimensions (EQ-5D) is a health questionnaire [19]. This scale is a standardized instrument for use as a measure of health outcome. Scores range from 0 to 1, with 1 indicating perfect health. It also includes a 0 to 100 VAS to assess general health. This will be recorded at all data collection time points.

Analgesic consumption will be recorded at each time point. This will include the daily dose of each analgesic. Each medication will be classified as “strong opioid”, “mild opioid” or “non-narcotic analgesic” according to opioid comparative information published in the Australian Medicines Handbook [20]. The opioids classified as “strong” include oxycodone, morphine, fentanyl, pethidine, hydromorphone, buprenorphine and tramadol. The opioids classified as “mild” include medications containing codeine or dextropropoxyphene. The non-opioid medications include paracetamol and non-steroidal anti-inflammatory drugs (NSAIDs). The patient will be given a score of 0, 1 or 2 in each of these three analgesic medication categories depending on the number of concurrent different medications being taken within each category. If the patient is taking two different “strong” opioid preparations, for example one prolonged release and another for breakthrough pain, then the score in the strong narcotic category will be 2. If the patient is using one strong opioid medication the score in this category will be 1. If the patient is taking no “mild” narcotics the score in that category is zero. If the patient is taking either paracetamol or an NSAID, then the score in that category will be 1 and if taking both it will be 2. The scores obtained in each of these three categories will be compared between the control and vertebroplasty groups. It is our hypothesis that the “strong opioid” scores in the vertebroplasty group will be lower than those of the control group.

In addition the daily opiate dose will be converted into a morphine dose equivalent using the Opioid Dose Equivalence, Calculation of oral Morphine Equivalent Daily Dose oMEDD) [21], published by the Faculty of Pain Medicine which is a faculty of the Australian and New Zealand College of Anaesthetists. The morphine equivalent daily dose at each data point will be compared between placebo and vertebroplasty groups.

Questions regarding perceived pain change after procedure, blinding and perception of treatment assignment will be administered at 3 days and 2 weeks. A timed get up and go test [22], which is a measure of function in older people, will be performed during clinic visits at baseline, 2 weeks and 6 months. Questions regarding duration of hospitalization, resource use and health care utilization will be collected at 6 months.

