### Analysis

Effectiveness analyses will be by the intention-to-treat principle, whereby patients are analysed according to the study arm to which they were randomized regardless of the treatment actually received, and toxicity analyses will be according to treatment received. Proportions will be compared using a two-sided chi-squared or exact (conditional binomial) test. Changes in quality of life measures (pain and functional disability scores) will be analysed using *t*-tests to enable comparisons with published studies, and non-parametric tests or regression modelling techniques depending on the distribution of the data. All comparisons will be two-sided with a significance level of 5% considered as being statistically significant. Measures of effect will be presented as either risk differences, odds ratios or mean differences together with the respective 95% confidence intervals.

The primary end point is the proportion of patients whose NRS pain score reduces from 7/10 (or more) to 4/10 (or less) at 14 days. The study sample size is sufficient to detect an absolute difference of 30% in favour of the vertebroplasty arm. Sub-group analysis will also be performed on three different regions of the spine: thoracic (T4 to T10), thoraco-lumbar (T11 to L2) and lumbar (L3-L5). Those patients with two acute fractures involving more than one of these regions will be excluded from this sub-group analysis. We hypothesize that the vertebroplasty efficacy will be maximal in the thoracolumbar group. We expect the benefit will be greater in thoraco-lumbar fractures than in thoracic and lumbar fractures. We hypothesize that the primary end point (pain score <4/10 at 2 weeks) will be achieved in more than 30% additional patients (than control) in the thoraco-lumbar fractures and in less than 30% additional patients (than control) in the thoracic group and the lumbar group. Note that the trial is not specifically powered for this sub-group analysis, and the statistical conclusions that can be drawn from the sub-group analysis will be limited by the number of patients in each sub-group.

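### Opioid dose and analgesic scores are compared between arms with no stated use of the recorded baseline: valid, but less precise than the collected data allow

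*Protocol article*

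**What the plan says.** The Measures section, in the paragraphs on analgesics after Table 2, sets out two outcomes. Each patient gets a score of 0, 1 or 2 in each of three drug categories, and "The scores obtained in each of these three categories will be compared between the control and vertebroplasty groups". For the strong-opioid category a direction is predicted: "scores in the vertebroplasty group will be lower than those of the control group". Daily opioid dose is also converted to oral morphine equivalents, and "The morphine equivalent daily dose at each data point will be compared between placebo and vertebroplasty groups". No test, model, covariate or change from baseline is named for either outcome.

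The baseline values exist. The Baseline assessment section lists "QUALLEFFO quality of life, medication usage and EQ-5D" among the items collected, Table 2 marks pain medication at baseline and at all five later contacts, and the Measures section says "Analgesic consumption will be recorded at each time point. This will include the daily dose of each analgesic".

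The Analysis section gives a rule that does use baseline, but for other outcomes: "Changes in quality of life measures (pain and functional disability scores) will be analysed using" t-tests, or non-parametric or regression methods depending on the distribution. Its parenthesis names pain and functional disability, not analgesics.

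Under Random allocation, the minimization factors are age, degree of height loss, trauma, steroid use and site. Opioid use at entry is not among them.

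**The concern.** What a patient takes before the procedure is likely to predict what the same patient takes afterwards. If so, part of the spread in follow-up dose is already explained by a value the trial holds, and a comparison that leaves that value out carries avoidable noise. Because allocation does not balance entry opioid use, a chance difference between arms at baseline also passes in part into the follow-up comparison.

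This matters somewhat more than for an ordinary secondary outcome. The Discussion acknowledges that a patient-rated pain score can be influenced by opioid use, and it presents analgesic use as a more objective, though indirect, measure. A noisier opioid comparison weakens that support for a subjective primary endpoint. At stake is the chance of detecting a real reduction in analgesic use, and how closely its size can be estimated.

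**Working it through.** **The plan's own figure.** The only stated power (Sample size section) is for the primary outcome: 35% versus 65%, 60 per arm, two-sided 5%, above 80%. With mean proportion 0.5, z = (0.30 − 1.96·√(2·0.25/60)) / √((0.35·0.65 + 0.65·0.35)/60) = (0.30 − 0.1789)/0.0871 = 1.39, so power is 91.8% (88.5% with continuity correction). The claim reproduces, and this point does not affect it. No figure is given for dose or scores.

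**Inputs.** From the document: n = 60 per arm, two-sided 5%. Assumed, because the document is silent: a true difference of 0.4 SD in follow-up dose, and a baseline to follow-up correlation r between 0.2 and 0.7. A normal model is used as a guide.

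**Formulas.** In SD units, the standard error of the arm difference is:
- follow-up value alone: √(2/60) = 0.1826
- adjusted for baseline: 0.1826·√(1 − r²)
- change from baseline: 0.1826·√(2(1 − r))

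Power = Φ(0.4/SE − 1.96). For the unadjusted comparison, 0.4/0.1826 − 1.96 = 0.231, which gives 59%. For the adjusted comparison at r = 0.5, SE = 0.1826·0.866 = 0.1581 and 0.4/0.1581 − 1.96 = 0.570, which gives 72%.

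| r | Unadjusted | Baseline-adjusted | Change score | Unadjusted n per arm matching 60 adjusted, 60/(1 − r²) |
|---|---|---|---|---|
| 0.2 | 59% | 61% | 41% | 62.5 |
| 0.3 | 59% | 63% | 46% | 66 |
| 0.5 | 59% | 72% | 59% | 80 |
| 0.7 | 59% | 87% | 81% | 118 |

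The difference detectable with 80% power is (1.96 + 0.842)·0.1826 = 0.51 SD unadjusted. Adjusted, it is 0.50, 0.49, 0.44 and 0.37 SD at the four values of r.

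**Change score.** Its variance factor 2(1 − r) exceeds 1 whenever r < 0.5, so below that value it does worse than ignoring baseline. Since (1 − r²) ≤ 2(1 − r) for every r, adjustment is never less precise than a change score in this model.

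**Validity.** In 10,000 simulated trials per setting with no true effect, the unadjusted comparison had a mean estimate within 0.003 SD of zero and rejected in 5.0%, 4.8% and 4.7% of trials at r = 0.3, 0.5 and 0.7. With a true difference of 0.4 SD, simulated power was 58% to 59% unadjusted and 62%, 71% and 86% adjusted, in line with the table.

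**Chance imbalance.** A baseline difference between arms has standard deviation 0.183 SD, so its 95% range is ±0.36 SD. A share r carries into the unadjusted estimate: at the edge of that range, about 0.11, 0.18 and 0.25 SD at r = 0.3, 0.5 and 0.7.

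**The case against.** The strongest reply is that a journal article condenses the plan. The sentences sit under Measures, say what is compared and when, and name no model. A comparison of dose at a visit is compatible with a covariate-adjusted analysis, and the covariates for a secondary outcome may be in an analysis plan that is not shown. This stands to the extent that a reader who infers that the plan rules out baseline adjustment goes further than the text. It does not remove the point. The article does fix the compared quantity as the level of dose, it applies change from baseline to other outcomes, and stating the adjustment costs nothing.

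Several stronger readings are tempting and should not be made:

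- *That the comparison is biased or inflates false positives.* It is not, and does not. Given a chance imbalance of exactly 0.3 SD, the unadjusted false-positive rate is about 8%, 11% and 13% at r = 0.4, 0.6 and 0.7. But only about 10% of trials this size exceed that imbalance (0.3/0.1826 = 1.64), and with no imbalance the rate falls below 5% (about 1.4% at r = 0.6). These average to 5%.
- *That the dose outcome carries the stated hypothesis.* The hypothesis belongs to the strong-opioid score. Likewise, the wording about every data point is attached to dose, not to the scores.
- *That entry opioid use is unrestricted.* Table 1 excludes patients whose chronic back pain needs opioids. This may narrow the spread of baseline dose. No limit is shown on opioids taken for the acute fracture.
- *That a significance test at baseline is planned.* Baseline is one of the data points, but the sentence can equally mean showing dose by arm at each visit. No baseline test is clearly announced.

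**Conclusion.** The point holds as a minor efficiency and clarity matter on a secondary outcome. As written, neither the dose comparison nor the score comparison uses the baseline medication data, and adjustment would gain precision whenever r is above 0.

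The size cannot be fixed from the document. At 60 per arm and an assumed 0.4 SD effect, the gain runs from about 2 percentage points of power (r = 0.2) to about 27 (r = 0.7). With fracture pain of under six weeks at entry, r may well be lower at 6 months than at day 3 or day 14. The normal model is only a guide: doses are likely to be skewed with zeros, and the category scores take three values, for which no separate power was computed. The primary endpoint, the sample size and every stated figure are unaffected.

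**What to change.** In the analgesic paragraphs of the Measures section (or in the analysis plan, if it does not already say so), replace the plain between-arm comparison with wording such as:

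*Post-baseline morphine-equivalent daily dose (day 3 to 6 months) will be compared between arms adjusted for baseline morphine-equivalent dose, using rank-based ANCOVA or ANCOVA on log(dose + 1). Each analgesic category score will be compared between arms adjusted for its own baseline score, using an ordinal model. Baseline values will be described by arm and not tested.*

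One of the two dose methods should be chosen in advance, and the choice recorded before outcomes are examined by arm. Simple change from baseline should not be used instead, for the reason shown in the working.

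The cost is a sentence or two of analysis wording. It needs no new data, no extra patient contact and no change to the sample size.
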